## Abstract

**Background:**

Quadriplegia is a severe, catastrophic injury that predominantly affects people early in life, resulting in lifelong physical disability. Obstructive sleep apnoea is a direct consequence of quadriplegia and is associated with neurocognitive deficits, sleepiness and reduced quality of life. The usual treatment for sleep apnoea is nasal continuous positive airway pressure (CPAP); however, this is poorly tolerated in quadriplegia. To encourage patients to use this therapy, we have to demonstrate that the benefits outweigh the inconvenience. We therefore propose a prospective, multinational randomized controlled trial of three months of CPAP for obstructive sleep apnoea after acute quadriplegia.

**Methods/design:**

Specialist spinal cord injury centres across Australia, New Zealand, the UK and Canada will recruit medically stable individuals who have sustained a (new) traumatic quadriplegia (complete or incomplete second cervical to first thoracic level lesions). Participants will be screened for obstructive sleep apnoea using full, portable sleep studies. Those with an apnoea hypopnoea index greater than 10 per hour will proceed to an initial three-night trial of CPAP. Those who can tolerate CPAP for at least 4 hours on at least one night of the initial trial will be randomized to either usual care or a 3-month period of auto-titrating CPAP. The primary hypothesis is that nocturnal CPAP will improve neuropsychological functioning more than usual care alone. The secondary hypothesis is that the magnitude of improvement of neuropsychological function will be predicted by the severity of baseline sleepiness measures, sleep fragmentation and sleep apnoea. Neuropsychological tests and full polysomnography will be performed at baseline and 3 months with interim measures of sleepiness and symptoms of autonomic dysfunction measured weekly. Spirometry will be performed monthly. Neuropsychological tests will be administered by blinded assessors. Recruitment commenced in July 2009.

**Discussion:**

The results of this trial will demonstrate the effect of nocturnal CPAP treatment of obstructive sleep apnoea in acute quadriplegia. If CPAP can improve neurocognitive function after injury, it is likely that rehabilitation and subsequent community participation will be substantially improved for this group of predominantly young and severely physically disabled people.

**Trial registration:**

Australian New Zealand Clinical Trial Registry
ACTRN12605000799651

## Background

Spinal cord injury (SCI) is one of the most severe disabilities a person may sustain. The resultant loss of physical independence can lead to a significant requirement for assistance with personal care and activities of daily living, with consequent loss of privacy and compromised autonomy. The cost to the individual in terms of vocational opportunities and achievements can be extremely high. The cost to the community, in terms of lost work capacity, reduced ability to utilize prior education and training and the financial costs of disability pensions, carers’ pensions, attendant care, respite care, equipment and environmental adaptations, is associated with burden and reduced quality of life. In Australia, the annual incidence of SCI is approximately 15 per million
[1,2]. Therefore, each year in Australia 260 people sustain a SCI and of these 57% will lose full function in their arms and legs (quadriplegia).

Quadriplegia affects 130 to 150 people per year in Australia
[3]. The lifetime costs of the injury are substantial, even though the numbers affected are relatively small. In 2009, Access Economics estimated the lifetime healthcare cost of each incident case of quadriplegia in Australia to be $9.5million, with the total cost of SCI estimated at $2.0 billion
[3]. The majority of SCI patients sustain their injuries in their second or third decade of life. If those who do not survive the first year following injury are excluded from analysis, then life expectancy approaches that of the general population
[2]. Thus, if any secondary disease or impairment were a direct consequence of the SCI, it would have a significant effect for many years. Obstructive sleep apnoea (OSA) is such a condition.

The prevalence of sleep-disordered breathing, predominantly OSA, in quadriplegia is two to five times higher
[4-11] than in the general population
[12]; however, the reasons for this increased prevalence remain unclear. A prospective longitudinal examination of the sleep and breathing of all new patients with acute quadriplegia who attended a specialist spinal unit over an 18 month period found a prevalence of OSA of up to 83% in the first year after injury
[13]. Sleep and respiratory studies were performed immediately after acute quadriplegia in 30 subjects (25 men) and at 2 weeks and 1, 3, 6 and 12 months post injury. Three subjects (10%) had probable OSA before their injury. However, 60% had OSA by 2 weeks after injury, 83% at 3 months and 62% at 1 year. These findings have been confirmed in another centre
[14]. It is thus apparent that that the prevalence of OSA was extremely high in the first year after injury and that OSA is a direct consequence of acute quadriplegia.

Untreated OSA is a significant issue for those with quadriplegia. Previous authors have demonstrated that OSA in quadriplegia results in significant neurocognitive deficits
[15]. Sajkov *et al*. demonstrated that hypoxia during sleep in subjects with quadriplegia and untreated OSA was associated with deficits in attention, concentration, memory and learning. Further, the neurocognitive impairments were both statistically and clinically significant in people with both quadriplegia and OSA, when compared with normal population values. These deficits are likely to prolong rehabilitation substantially, reducing future independence and limiting vocational outcomes following injury.

The usual treatment for OSA is continuous positive airway pressure (CPAP), which corrects sleep hypoxia and improves neurocognitive performance
[16] and nocturnal blood pressure control
[17] in the able-bodied with OSA. Reports of CPAP treatment in quadriplegia in uncontrolled studies are disappointing, with low levels of compliance with therapy reported. Stockhammer *et al*.
[10] found 31 cases of sleep-disordered breathing after screening 50 subjects with quadriplegia. Only 16 of the 31 had previously used CPAP, with 11 (35%) continuing to use the device for at least a few weeks. Burns *et al*. undertook a cross-sectional postal survey of patients of a US Veterans Affairs Spinal Cord Service whose record indicated diagnosis or treatment for OSA
[18]. Of those identified, only 39% were using CPAP at the time, while an additional 27% had used CPAP but had discontinued therapy owing to intolerance. In our previously described cohort study
[13], five of the subjects were suspected clinically of having OSA and treatment with CPAP was offered. Only one of the subjects continued with CPAP for more than a few days, and that subject only did so after a period of respiratory failure. The reasons for this poor adherence are multifactorial, but the most commonly reported complaints are nasal congestion, an inability to fall asleep with the mask on and a lack of perceived benefit or noticeable change in symptoms.

In summary, it is known that OSA is a direct consequence of acute quadriplegia and that it is associated with cognitive deficits likely to impair rehabilitation after injury. Moreover, although CPAP is the usual treatment for OSA, it is poorly tolerated in quadriplegia. If the detection, treatment and adherence to CPAP therapy are to be improved in these patients, further research is vital. We propose to perform a prospective multicentre randomized controlled trial of CPAP for OSA after acute quadriplegia.

In preparation for this trial, the Melbourne research team completed a one-year feasibility study of this project
[19]. The primary aim of the feasibility study was to determine the feasibility of CPAP treatment for OSA following acute quadriplegia. All patients (*n* = 44) with new quadriplegia who presented to the Austin Hospital during the nine months of study recruitment were eligible for study inclusion. Participants were tested for OSA with the Somté PSG (Compumedics, Abbotsford, Australia) and those with OSA were offered treatment with an auto-titrating CPAP device for three months. Rates of patient accrual, enrolment and OSA experienced during the study accurately reflected initial estimates. The feasibility study findings suggested that this current trial would confirm that OSA is associated with significant sub-acute morbidity and that CPAP treatment will be associated with an improvement in clinical outcomes.

The specific aim of the COSAQ study is to determine the effect of nocturnal auto-titrating CPAP treatment on neuropsychological function, quality of life, autonomic dysfunction and breathing in people with acute quadriplegia and OSA. To address this aim, one primary and two secondary hypotheses were developed and will be tested. The primary hypothesis is that usual care and nocturnal CPAP treatment will improve neuropsychological functioning more than will usual care alone; specifically, working memory as tested on the Paced Auditory Serial Addition Test (PASAT). The first secondary hypothesis is that the magnitude of improvement in neuropsychological function will be predicted by the severity of baseline sleepiness (Karolinska Sleepiness Scale (KSS)), sleep fragmentation (Sleep Efficiency, Arousal Index) and sleep apnoea (apnoea hypopnoea index (AHI), percentage total sleep time with SpO_2_ < 90%). The second secondary hypothesis is that usual care and nocturnal CPAP will improve the following parameters more than usual care alone:

1. Sleepiness and symptoms: Karolinska Sleepiness Scale (KSS) and the Basic Nordic Sleep Questionnaire (BNSQ).

2. Lung Function: spirometry.

3. Quality of life: Assessment of Quality of Life (AQoL).

4. Autonomic dysfunction: event diary and heart rate variability.

5. Health utility: AQoL-derived change in utility and associated quality-adjusted life years (QALY).

6. Depression and anxiety: Hospital Anxiety and Depression Scale (HADS) and the Profile of Mood States (POMS).

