### Estimated subject numbers

This is a three-month treatment trial at a time where there is profound disruption in the life of the study participants. Over this acute period, direct measurements of quality of life and performance in rehabilitation will not demonstrate the efficacy or otherwise of CPAP. The feasibility study clearly demonstrated that there was substantial variability in quality of life post injury, unrelated to OSA or CPAP, thus rendering these outcomes unsuitable for demonstrating short-term improvement in a study sample of constrained size. We are, therefore, basing our sample size calculations on neurocognitive performance, a number of measures of which form our test battery. The specific neurocognitive test in the test battery, which is best characterized in both the spinal population and OSA, is the PASAT. Lower (worse) PASAT scores correlate with sleep fragmentation severity in the able-bodied
[31] and OSA severity in quadriplegia
[15]. Lower PASAT scores are also associated with diminished frontal lobe function, as assessed by functional magnetic resonance imaging
[32] and a mean difference in PASAT scores of seven discriminates between those with and without cognitive impairment in multiple sclerosis
[33]. In the able-bodied with OSA, those adherent to CPAP over three months have a PASAT score 18 units higher than those who are not (standard deviation of 33)
[34].

Assuming a mean difference between the study arms of 18
[34], a standard deviation of 33, a power of 0.8, an *α* value of 0.05 and a nonadherence to CPAP rate of 15%, 150 subjects will be randomized. To ensure that 150 participants complete the study, we estimate that approximately 820 admissions with quadriplegia will be required across our collaborating centres (at least 8 of 44 admissions will meet the inclusion criteria, fail to meet the exclusion criteria, agree to participate, have OSA and tolerate CPAP). This sample is also adequate to detect any true difference between secondary outcomes, such as sleepiness (KSS number required = 44).

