### Statistical analyses

Usage data from the CPAP devices will be described and subjects classified as adherent, as described. The proportion of subjects continuing to use CPAP over the three months of treatment will be plotted and examined using survival (Kaplan-Meier) analysis. Statistics describing the distribution of CPAP usage, average numbers of hours used per night, and so on, will be calculated.

Changes in neurocognitive performance, AQoL, BNSQ and KSS will be examined with paired *t* tests, repeated measures analysis of variance and generalized linear mixed models, as appropriate. The rate of autonomic dysreflexia and the time course of development will be compared with *χ* squared and mixed model regression modelling as appropriate. Exploratory linear and logistic regression modelling will be performed to determine whether the average number of hours used or the likelihood of adherence can be predicted by any of the groups’ baseline characteristics.

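### The first secondary hypothesis is worded as a prognostic association with no usual-care comparison, so it can be confirmed even if CPAP has no effect

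*Protocol article*

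**What the plan says.** The Background gives the aim, which "is to determine the effect of nocturnal auto-titrating CPAP treatment on neuropsychological function" and on several other outcomes, and says that one primary and two secondary hypotheses were developed to address it.

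- The primary hypothesis is comparative: CPAP added to usual care should improve neuropsychological function, specifically the PASAT, more than usual care does.
- The second secondary hypothesis is comparative too: "usual care and nocturnal CPAP will improve the following parameters more than usual care alone".
- The one between them, the first secondary hypothesis, is not. It holds that "the magnitude of improvement in neuropsychological function will be predicted by the severity of baseline sleepiness" (KSS), sleep fragmentation (sleep efficiency, arousal index) and sleep apnoea (AHI, percentage of sleep time with saturation below 90%). That makes five predictors.

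The abstract's Methods/design paragraph repeats it, again without a comparison: "the magnitude of improvement of neuropsychological function will be predicted by the severity of baseline sleepiness measures, sleep fragmentation and sleep apnoea".

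Under Statistical analyses, neurocognitive change is to be examined with paired t tests, repeated measures analysis of variance and generalized linear mixed models, as appropriate. Exploratory linear and logistic regression is to "determine whether the average number of hours used or the likelihood of adherence can be predicted by any of the groups’ baseline characteristics". Mixed model regression is also named for autonomic dysreflexia.

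**The concern.** A statement that severity predicts improvement is about prognosis. A statement that severity changes the effect of CPAP is about benefit. Only the second needs a randomised control arm, and only the second addresses the aim. The hypothesis as written is the first kind.

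The two can come apart here. Under Estimated subject numbers, the article reports that lower PASAT scores go with sleep fragmentation severity in the able-bodied and with "OSA severity in quadriplegia". More severely affected participants may therefore start lower, and regression to the mean, practice or natural recovery could then link severity to larger gains in both arms. An analyst who regressed improvement on severity, pooled or in the CPAP arm alone, would be following the wording faithfully. A positive result could then be read as showing who benefits from CPAP, although usual care might show the same pattern.

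**Working it through.** **Wording.** Of the three hypotheses, the primary and the second secondary name usual care as comparator. The first secondary names neither an arm nor a comparator, in the Background or in the abstract. The only outcomes that Statistical analyses says will be regressed on baseline characteristics are hours of CPAP use and likelihood of adherence. No stated model explicitly relates baseline severity to cognitive change.

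**Inputs.** From Estimated subject numbers: difference 18, SD 33, power 0.8, α 0.05, nonadherence 15%, 150 randomised. Assumed: two-sided tests and 1:1 allocation (75 per arm). Also assumed, because the article gives no value: the correlation r between severity and PASAT change, taken as equal in both arms.

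**The article's own figure.** Diluting the effect for nonadherence gives 18 × 0.85 = 15.3. Then n per arm = 2 × (1.960 + 0.842)² × 33² / 15.3² = 73.03, rounded up to 74, so 148 in total. This reproduces 150 closely, so the sample size is not at issue.

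**Chance of confirming the hypothesis with no CPAP effect.** By the Fisher approximation, the test statistic for a correlation has mean atanh(r) × √(n − 3).

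- r = 0.1, pooled: 0.1003 × √147 = 1.22, and P(Z > 1.96 − 1.22) ≈ 23%.
- r = 0.1, CPAP arm: 0.1003 × √72 = 0.85, and P(Z > 1.96 − 0.85) ≈ 13%.
- r = 0.3, pooled: 0.3095 × √147 = 3.75, and P(Z > 1.96 − 3.75) ≈ 96%.
- r = 0.3, CPAP arm: 0.3095 × √72 = 2.63, and P(Z > 1.96 − 2.63) ≈ 75%.

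A simulation of least-squares regression of change on standardised severity (4,000 runs per setting, no CPAP effect of any kind) agrees:

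| Assumed r | Change on severity, pooled (n = 150) | Change on severity, CPAP arm (n = 75) | Arm × severity interaction |
|---|---|---|---|
| 0 | 4% | 5% | 5% |
| 0.1 | 23% | 14% | 5% |
| 0.2 | 70% | 40% | 6% |
| 0.3 | 97% | 76% | 5% |

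These rates are per predictor. Restricting the analysis to the CPAP arm lowers them only because n is smaller; it does not separate prognosis from benefit.

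**What the interaction test can detect.** Per SD of severity, with residual SD 33 and no covariate adjustment, SE = 33 × √(1/75 + 1/75) = 5.39. The change in CPAP effect detectable with 80% power is 2.80 × 5.39 ≈ 15.1 points per SD, about as large as the diluted main effect of 15.3. At half that effect, 7.65 points per SD, 7.65 / 5.39 = 1.42 and power is about 30%. Adjusting for baseline score would reduce the SE to the extent that baseline predicts the end-study score; the article gives no figure for this.

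**The case against.** The strongest reply is that the wording has a natural charitable reading. The sentence directly follows the primary hypothesis, so the improvement it mentions may mean improvement attributable to CPAP, which would already be effect modification. That reading is possible, but the text does not fix it, and the abstract repeats the sentence without the comparison.

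The second reply is that model terms belong in a fuller protocol or an analysis plan that is not shown. That stands, and the point does not rest on missing model detail. A reader might infer that the planned regressions cover only CPAP hours and adherence, or that the control arm will be left out of this analysis. The article supports neither inference. It names generalized linear mixed models for neurocognitive change, which could carry an arm-by-severity term, and mixed model regression for autonomic dysreflexia. It nowhere says that this hypothesis will be tested in one arm or pooled without arm.

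Third, the false-confirmation rates assume a regression of raw change on severity. If severity acted only through the baseline score, adjusting for baseline PASAT would remove the spurious association without an interaction. That also stands. But baseline adjustment does not separate prognosis from benefit if severity relates to recovery itself, in either direction.

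Finally, a reader might infer that a positive finding would steer CPAP towards severe or sleepy patients. The article does not propose this: under Follow-up at trial completion, devices are given or offered to both groups with no reference to severity.

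**Conclusion.** The concern holds as a limited point about the wording of one secondary hypothesis. As stated in the Background and the abstract, it can be true with no CPAP effect, so confirming it would not address the trial's aim.

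How often that would happen cannot be fixed from the article. The ranges of 23% to 97% pooled and 14% to 76% in the CPAP arm rest on assumed correlations of 0.1 to 0.3, equal arms, two-sided 5% tests and no adjustment for baseline score. The article reports correlations of PASAT with sleep fragmentation and OSA severity without coefficients, and none with KSS, so one value of r need not apply to all five predictors. That the interaction test stays at about 5% does not depend on r, provided that r is the same in both arms.

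**What to change.** Reword the hypothesis in the Background and the abstract along these lines: the difference between CPAP and usual care in neuropsychological function, PASAT first, varies with baseline sleepiness, sleep fragmentation and apnoea severity.

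State the test: in all randomised participants as allocated, regress end-study score on arm, baseline score, the severity measure (kept continuous) and arm × severity. Report each interaction estimate with its 95% confidence interval and label the set exploratory. A multiplicity adjustment such as Holm over the five predictors is optional under that label. If the prognostic question is also of interest, report it separately and name it as such.

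The change costs only wording and one model term per predictor, because the data are already being collected. The downside is statistical: the intervals will be wide and the interactions less likely to reach significance than a plain regression on severity.

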### Design

A prospective multicentre randomized controlled trial will be undertaken. The control group will receive usual care and the experimental group will receive 3 months of nocturnal CPAP using an auto-titrating CPAP device. The trial is being conducted in 10 specialist SCI units in Australia, New Zealand, the UK and Canada. Ethical approval has been obtained from the Human Research Ethics Committee at each site and at the Austin Hospital (EC00204). Informed consent will be provided prior to recruitment and participation. Subject recruitment commenced at Austin Health in July 2009 and subsequently at the other sites, as they became ready. Recruitment is scheduled to finish mid-2015.

### Participants

Participants will be recruited from consecutive admissions at the trial sites.

### Inclusion criteria

•Acute, traumatic quadriplegia (T1 or higher lesion, complete or incomplete).

•Older than 18.

### Exclusion criteria

•Successful CPAP therapy for OSA prior to injury.

•Significant head injury (Glasgow Coma Score < 8 at first assessment).

•Ongoing hypercapnic ventilatory failure (PaCO_2_ > 45 mmHg at time of consent).

•Probable inability to be followed up until three months.

•Condition likely to significantly limit CPAP use (for example, major psychoses, facial or base of skull fractures).

### General testing procedures

All testing will be performed at the participants’ bedsides. The respiratory function, questionnaires and other subjective data are collected at the same time in the mid-afternoon for each subject, to control for possible circadian influences. Sleep studies will commence at the subject’s usual bedtime. Figure 
1 illustrates the study recruitment and data collection flowchart.

**Figure 1 F1:**
[figure not shown]
Flowchart of COSAQ study participant flow.

